### Echocardiography core lab

Digital imaging and communication in medicine (DICOM) files of the echocardiograms generated at years 1 and 5 will be collected for analysis by the Echo Core Laboratory to ensure unbiased and consistent analysis of the diagnostic data and, by using serial echocardiographic studies conducted on the same patient, for evaluating changes in patient status over the course of the registry.

### Monitoring

Physicians/surgeons and study personnel are required to make themselves familiar with the registry protocol, eCRF, requirements and procedures. Approximately 20% of sites will be selected at random and monitored. In these centers, source data verification will be performed for all patients.

### Statistical analysis

The study sample size was determined based on feasibility considerations. Furthermore, 95% confidence intervals (CIs) for the primary endpoint at different event rates were determined and taken as a basis for the final sample size. It was estimated, from the COMMENCE Trial dataset where all-cause mortality was determined to be 1.2% at year 1 and 2.0% at year 2 [20], that 500 patients will arrive at a 95% confidence interval (CI) of ±0.87 for a 1% observed event rate and ± 1.50 for a 3% observed event rate.

Statistical analyses will be performed for the total study population and for the subgroups defined by baseline comorbidities if applicable. Continuous variables will be presented as mean ± standard deviation (SD) or as median with interquartile range (IQR), and categorical variables (e.g., gender) will be reported as frequencies and percentages. The Kolmogorov-Smirnov test will be used to test for normal distribution. Accordingly, comparisons will be performed using Student’s t-test or Mann-Whitney U test for continuous variables. The Chi-Square or Fisher exact test will be used for categorical variables. Linearized rates and actuarial probability statistics may be used where appropriate for adverse event reporting. Kaplan-Meier analyses will be performed for survival and safety outcomes. All statistical analyses will be performed using IBM SPSS Statistics version 24 (IBM, Armonk, New York) or R Core Team (https://www.R-project.org/), with a *p*-value of < 0.05 considered statistically significant.

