	**Hemodynamic performance and durability**
	• Hemodynamic performance of the INSPIRIS RESILIA Aortic Valve™ in the overall study population and stratified according to the different patient subgroups including patient prosthesis mismatch (PPM) including maximum (Pmax) and mean (Pmean) pressure gradient across the valve, Velocity Time Integral (VTI), Prosthesis Opening Area (EOA), Left Ventricular ejection fraction (LVEF), Paravalvular Leak
	• Severe hemodynamic structural valve deterioration (SVD) following Salaun [19]
	• Description of potential ViV procedures* and clinical outcome including follow-up
	**Clinical outcomes** (overall study population and stratified according to the different patient subgroups)
	• NYHA functional class compared to baseline
	• Freedom from valve-related rehospitalization
	• New pacemaker implantation
	• Freedom from valve-related complications
**Exploratory endpoints**	**Safety (defined according to VARC-2)**
	• SVD
	• Non-structural valve deterioration
	• Thromboembolic events (e.g., stroke)
	• Valve thrombosis
	• All bleeding/hemorrhage
	• Major bleeding/hemorrhage
	• All paravalvular leakage
	• Endocarditis
	• All-cause mortality
	• Cardiac-related mortality
	• Valve-related mortality
	• Re-intervention
	• Conduction disturbances

*Legend:* NYHA, New York Heart Association; SVD, structural valve degeneration; VARC, Valve Academic Research Consortium; ViV, valve-in-valve. *Valve-in-valve procedures include both transcatheter aortic valve implantations (TAVI) in surgical aortic valve replacements (SAVR) and SAVR in SAVR replacements

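### A normality pre-test chooses between Student's t and Mann-Whitney, and the tests named do not fit within-patient change: a low-severity point that is cheap to repair

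*Protocol article*

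**What the plan says.** The Statistical analysis section of the protocol article fixes a two-step rule for continuous variables. First, "The Kolmogorov-Smirnov test will be used to test for normal distribution". Then: "Accordingly, comparisons will be performed using Student’s t-test or Mann-Whitney U test for continuous variables". For the rest, "The Chi-Square or Fisher exact test will be used for categorical variables". The threshold is p < 0.05; sidedness is not given, and two-sided is assumed here. On scope, the section says: "Statistical analyses will be performed for the total study population and for the subgroups defined by baseline comorbidities if applicable". It names no unequal-variance test and no paired or repeated-measures method.

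Two other places plan comparisons of a patient with himself or herself. Table 1 (Objectives) lists "NYHA functional class compared to baseline" among the secondary clinical outcomes. The Echocardiography core lab section describes its work as done "by using serial echocardiographic studies conducted on the same patient, for evaluating changes in patient status over the course of the registry". Table 2 schedules NYHA class at baseline and years 1, 3 and 5, and echocardiography at those visits and at discharge.

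**The concern.** There are three linked points.

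- **Choice by pre-test.** Student's t compares means; Mann-Whitney compares ranks. A normality test rejects more often as the sample grows, so the same gradient could be compared on means for one comorbidity and on ranks for another, partly because of group size.
- **Student's rather than Welch's t.** Groups with and without a comorbidity may differ in both size and spread. The pooled variance is then wrong, and a normality test does not detect this.
- **Pairing.** Mann-Whitney, chi-square and Fisher are independent-group tests. Because Mann-Whitney is the named alternative, Student's t reads most naturally as the two-sample form. None of these uses the correlation between a patient's visits, and chi-square also ignores the order of the NYHA classes.

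At stake is how reliable and comparable the secondary hemodynamic and functional results by comorbidity will be. Those contrasts are central to the registry's purpose.

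**Working it through.** **The plan's own figure.** The only design figure is the precision for mortality with 500 patients. 1.96 × √(0.01 × 0.99 / 500) = 0.87 points and 1.96 × √(0.03 × 0.97 / 500) = 1.50 points, both as stated. It does not bear on this point.

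**Inputs.** From the article: 500 patients, the named tests, the 0.05 threshold. Not in the article, so assumed: group sizes, SD ratios, within-patient correlation r, and the shape of the data.

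**1. Student's t with unequal sizes and SDs (60 versus 440, SDs 1.5 and 1).**

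Type I error = 2[1 − Φ(1.96 × √(V_pooled / V_true))], where V_pooled = s²_p(1/n₁ + 1/n₂), V_true = σ₁²/n₁ + σ₂²/n₂, and 1/60 + 1/440 = 0.01894.

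- Larger SD in the smaller group: s²_p = (59 × 2.25 + 439 × 1)/498 = 1.148, so V_pooled = 0.02174. V_true = 2.25/60 + 1/440 = 0.03977. The ratio is 0.547, its root 0.739, and 1.96 × 0.739 = 1.449. **Type I error 14.7%.**
- Larger SD in the larger group: s²_p = (59 × 1 + 439 × 2.25)/498 = 2.102, so V_pooled = 0.03981. V_true = 1/60 + 2.25/440 = 0.02178. The ratio is 1.828, its root 1.352, and 1.96 × 1.352 = 2.650. **Type I error 0.8%.**

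Simulated type I error at nominal 5%, normal data (4,000 runs; the first group has the SD shown relative to the second):

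| Split | SD ratio | Student's t | Welch | Mann-Whitney |
|---|---|---|---|---|
| 50 / 450 | 1 | 4.8% | 4.8% | 5.0% |
| 50 / 450 | 1.5 | 15.1% | 4.9% | 9.1% |
| 100 / 400 | 1.5 | 12.6% | 5.6% | 8.7% |
| 250 / 250 | 1.5 | 5.1% | 5.1% | 5.1% |
| 400 / 100 | 1.5 | 1.4% | 5.1% | 2.6% |

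Imbalance alone does no harm, and nor do unequal SDs with equal group sizes. The distortion needs both.

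**2. The two-stage rule (Kolmogorov-Smirnov with Lilliefors p-values in each group, then t or Mann-Whitney; 800 runs).** With equal SDs and normal data the error was 4.8% (50 / 450) and 5.4% (100 / 400); with skewed data it was 4.9% for both. At SD ratio 1.5 with normal data it was 16.0% (50 / 450) and 11.1% (100 / 400). The pre-test therefore does not itself inflate the error, but it gives no protection against unequal variances.

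**3. Dependence of the pre-test on group size.** For gamma data with shape 4 (skewness 1), simulated rejection of normality was:

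| n | Uncorrected p-values | Lilliefors-corrected |
|---|---|---|
| 60 | 2–3% | 42–45% |
| 100 | 7–8% | 68–70% |
| 440 | 91–92% | 100% |

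The article does not say which version applies. Rejection rises with n under both, much more steeply without the correction.

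**4. Independent-group test on paired data.** The unpaired test takes the variance of the mean difference as 2σ²/n; the true value is 2σ²(1 − r)/n. Its statistic therefore has SD √(1 − r).

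- Type I error = 2[1 − Φ(1.96/√(1 − r))]. At r = 0.5 this is 2[1 − Φ(2.77)] = **0.6%**.
- If the paired test has 80% power (1.96 + 0.84 = 2.80), unpaired power = 1 − Φ(1.96/√(1 − r) − 2.80). At r = 0.5: 1 − Φ(−0.03) = **51%**. At r = 0.7: 1 − Φ(3.58 − 2.80) = 1 − Φ(0.78) = **22%**.

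A simulation of 400 pairs at r = 0.5 agrees: unpaired type I error 0.7% against 4.8% paired, and power for a 0.15 SD change of 60% against 87%.

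**The case against.** The strongest reply is that the article never assigns these tests to within-patient change. It speaks of the total population and the comorbidity subgroups, and then of comparisons. The natural reading is with versus without a comorbidity, where all four tests are standard. They also remain valid for comparing change scores between such groups. NYHA against baseline can be described with a shift table, the core lab section names no test, and Student's t has a paired form. Paired methods may stand in the full protocol or analysis plan, which a condensed article need not repeat.

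Most of this stands. A reader might infer that NYHA and echo change will be tested with the wrong error; the text does not say so. What remains is that the methods it names do not suit two analyses it plans.

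A reader might also infer that unbalanced comorbidity groups make the p-values invalid, or that false positives run at about three times the nominal rate. The document supports neither. It gives no group sizes or SDs, imbalance alone leaves the error at 5%, and 14.7% is one assumed scenario whose mirror image is 0.8%.

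The reply does not remove the pre-test rule or the choice of Student's t. Both are stated commitments, not omissions.

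**Conclusion.** The point holds as a low-severity, cheap improvement. The firm part is the stated rule: a normality test decides whether means or ranks are compared, and the t-test named assumes equal variances. The fault of the pre-test is the shifting estimand; with equal variances the two-stage rule kept about 5%. Student's t misstates the error only if groups differ in both size and variance, and then in either direction.

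The within-patient part is conditional. If the named tests are used on paired data with positive correlation, they are conservative and lose power; they do not create false positives. All sizes rest on assumed group sizes, SD ratios, correlations and distributions. The primary objective, all-cause mortality at 1, 3 and 5 years, does not depend on these tests.

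**What to change.** - Delete the normality pre-test.
- For continuous contrasts with versus without a comorbidity, fix Welch's t-test or regression with robust standard errors in advance.
- For change from baseline, name paired methods: Wilcoxon signed-rank or an ordinal mixed model for NYHA class, and a linear mixed model over the scheduled visits for gradients, EOA and LVEF, with the reference visit stated.

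If the full plan already names such methods, the article's wording only needs to be aligned with it. The cost is about two sentences and slightly more analysis work. No new data are needed.

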### Objectives

The primary objective of the study is to determine all-cause mortality at 1, 3, and 5 years after SAVR (Table 1). The secondary objectives are designed to assess the study population mortality, hemodynamics and durability of the prosthetic valve, and clinical outcomes. Study population mortality is defined as all-cause, cardiac- and valve-related mortality in the overall study population and in the following patient subgroups at all time points: patients with chronic kidney disease, diabetes, hypertension, metabolic syndrome and chronic inflammation. Assessment of hemodynamics and durability will include the hemodynamic performance of the INSPIRIS RESILIA aortic valve in the overall study population and stratified according to the different patient subgroups including patient prosthesis mismatch (PPM) including maximum (Pmax) and mean (Pmean) pressure gradient across the valve, velocity time integral (VTI), prosthesis opening area (EOA), left ventricular ejection fraction (LVEF) and paravalvular leak (PVL); severe hemodynamic SVD following Salaun [19]; and potential valve-in-valve (ViV) procedures and clinical outcome including follow-up. Clinical outcomes will be assessed in the overall study population and, in addition, will be stratified across the following patient subgroups: New York Heart Association (NYHA) functional class compared to baseline, freedom from valve-related rehospitalization, new pacemaker implant and freedom from valve-related complications. Exploratory safety endpoints are presented in Table 1.

**Table 1 Tab1:** Registry objectives

Primary objectives	To determine all-cause mortality 1, 3, and 5 years after surgery
**Secondary objectives**	**Mortality**
	To determine all-cause, cardiac- and valve-related mortality in the overall study population and in different patient subgroups at all timepoints:
	• Chronic kidney disease
	• Diabetes
	• Hypertension
	• Metabolic syndrome
	• Chronic inflammation

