### Data collection

The clinical outcome data collected will be based on the site’s standards of care for SAVR. The collected data will include medical history, physical assessments, safety parameters, electrocardiogram (ECG), laboratory results and transthoracic/transesophageal echocardiography (Table 2). Data will be captured by an electronic case report form (eCRF; Software for Trials Europe GmbH, Berlin, Germany) and data will be checked automatically for plausibility and completeness.

**Table 2 Tab2:** Data collection schedule

	Screening/baseline	Surgery	Discharge	Year 1	Year 3	Year 5
Medical history^1^	X					
Physical examination^2^	X		X	X	X	X
ECG (12-lead)	X		X	X	X	X
Echocardiogram (TTE)	X		X	X	X	X
Core Lab echo				X		X
NYHA class/CCS angina class	X			X	X	X
Medications	X		X	X	X	X
Procedural information		X				
Aetiology		X				
SAE reporting		X	X	X	X	X
Discharge data			X			
Rehospitalization data^3^				X	X	X
Return to work				X	X	X

^1^Includes cardiovascular and non-cardiovascular conditions, prior cardiac interventions and surgeries

^2^Physical examination, includes height, weight and vital signs (blood pressure and heart rate)

^3^Includes re-interventions, potential ViV procedures

*Legend:* CCS, Canadian Cardiovascular Society; ECG, electrocardiogram; NYHA, New York Heart Association; SAE, serious adverse event(s); TTE, transthoracic echocardiogram

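### The test rule has no route for ordered or paired data, so NYHA class compared with baseline defaults to Chi-Square or Fisher

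*Protocol article*

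**What the plan says.** The Statistical analysis section of the protocol article sets out two routes for comparisons. After a normality check, "comparisons will be performed using Student’s t-test or Mann-Whitney U test for continuous variables". For everything else, "The Chi-Square or Fisher exact test will be used for categorical variables". On the descriptive side, "categorical variables (e.g., gender) will be reported as frequencies and percentages". The significance threshold is a p-value of "< 0.05 considered statistically significant"; sidedness is not stated. There is no separate rule for ordered variables or for repeated measurements on the same patient.

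Table 1 lists, under clinical outcomes, "NYHA functional class compared to baseline". The table and the Objectives text place these outcomes in the overall population and in the comorbidity subgroups: "Clinical outcomes will be assessed in the overall study population and, in addition, will be stratified across the following patient subgroups". The data collection schedule (Table 2) records "NYHA class/CCS angina class" at baseline and at years 1, 3 and 5.

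**The concern.** NYHA class is an ordered four-level scale. It is not continuous, so under a two-route rule it lands with the categorical variables. Two things then go wrong.

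- **Order is lost.** Pearson Chi-Square or Fisher on a 2x4 table gives the same p-value however the four class labels are permuted. A consistent move towards worse classes is spread over 3 degrees of freedom, and the test gives neither a direction nor an effect estimate. Yet the registry's question about comorbidity and functional status is directional.
- **Pairing is lost.** A comparison with baseline is made within patients. An ordinary Chi-Square or Fisher test on visit by class treats the baseline and follow-up records as independent samples, although each patient supplies one of each.

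At stake is how well a secondary outcome is analysed in subgroups that may be small. The primary endpoint, all-cause mortality, is not affected.

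**Working it through.** **The plan's own figure.** The only precision stated is for mortality with 500 patients. The half-width is 1.96 x sqrt(p(1-p)/500):

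- p = 1%: 1.96 x sqrt(0.01 x 0.99/500) = 0.872 points (stated ±0.87)
- p = 3%: 1.96 x sqrt(0.03 x 0.97/500) = 1.495 points (stated ±1.50)

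Both are reproduced. They do not bear on NYHA, for which the article states no power target or effect size.

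**Which route applies to NYHA.** The rank test appears only as "Mann-Whitney U test for continuous variables". The one example of a categorical variable, gender, is nominal but is given only as an example, so it does not confine the rule to nominal data. No sentence names a test for NYHA. Its assignment to Chi-Square or Fisher is the default reading of the rule.

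**Illustration of the order problem.** All of these inputs are assumptions: 450 patients assessed; 75 to 200 with the comorbidity; classes I/II/III/IV of 65/28/6/1% or 50/37/11/2% in those without it; a common odds ratio (OR) of 1.6 to 2.0 for a worse class; two-sided 5%. The shift multiplies each cumulative odds by the OR. For 65/28/6/1% and OR 1.8:

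- class II or worse: 0.35/0.65 x 1.8 = 0.969, so 49.2%
- class III or worse: 0.07/0.93 x 1.8 = 0.135, so 11.9%
- class IV: 0.01/0.99 x 1.8 = 0.0182, so 1.8%

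The subgroup distribution is then about 50.8/37.3/10.1/1.8%. Simulated power of Pearson Chi-Square on the 2x4 table against the tie-corrected Mann-Whitney test, over both distributions and all subgroup sizes:

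| OR | Chi-Square | Mann-Whitney | Gain (points) |
|---|---|---|---|
| 1.6 | 37-58% | 46-74% | 9-17 |
| 1.8 | 54-80% | 67-92% | 11-14 |
| 2.0 | 70-92% | 81-97% | 5-12 |

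A repeat of these settings agreed within simulation error.

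**How far the gain depends on the assumptions.** With 400 or 500 patients, a subgroup share of 10 to 50%, four NYHA distributions and OR 1.3 to 2.5, the gain runs from about -1 to +18 points. Examples:

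- 400 patients, 10% share, 70/25/4.5/0.5%, OR 1.3: 14.2% for Chi-Square against 13.2% for Mann-Whitney
- 500 patients, 50% share, 50/35/12/3%, OR 1.5: 49.8% against 68.0%
- the same with OR 2.5: 99.9% against 100.0%

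**Where it reverses.** Take 50/35/12/3% against 50/25/20/5%, with 30% of 500 in the subgroup. Class I is equal, and the subgroup has fewer patients in II and more in III and IV. The rank test responds to the probability that a subgroup patient is in a worse class than a comparison patient, counting ties as half:

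- subgroup worse: 0.25 x 0.50 + 0.20 x 0.85 + 0.05 x 0.97 = 0.3435
- subgroup better: 0.35 x 0.50 + 0.12 x 0.75 + 0.03 x 0.95 = 0.2935
- ties: 1 - 0.3435 - 0.2935 = 0.363; result 0.3435 + 0.363/2 = 0.525

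That is close to the null value of 0.5, so power is 72% for Chi-Square and 18% for Mann-Whitney.

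**The pairing problem.** This needs no simulation. With n patients seen at baseline and year 1, a visit-by-class table holds 2n records from n patients. The ordinary Chi-Square and Fisher tests assume 2n independent records.

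**The case against.** The strongest reply is that this is a generic paragraph in a condensed article. It never mentions NYHA, and the full protocol or analysis plan may name an ordinal method. It is true that the assignment is by default, and a reader who inferred that the article expressly prescribes Chi-Square for NYHA would go too far. But the point is not that detail is absent: the rule as published confines the rank test to continuous variables, and so excludes it for an ordered outcome.

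Second, a reader might infer that this plan loses 5 to 17 points of power. The document does not support that. Every input is assumed, the proportional-odds setting favours the rank test, and the sign can reverse. The simulation also used Pearson Chi-Square only. With 65/28/6/1%, 75 in the subgroup and OR 1.8, the expected class IV total is 75 x 0.0179 + 375 x 0.01 = 5.09, which splits as 0.85 and 4.24. Both are below 5, where Fisher would usually be used, and its power was not computed.

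Third, it is tempting to extend the point to paravalvular leak grade and CCS class. The article lists paravalvular leak without grades, and CCS class is collected but is not a listed objective. Neither belongs here.

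Fourth, frequencies and percentages will show the direction beside any p-value. That softens the complaint about direction, but it supplies no estimate with a confidence interval.

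Last, the sample size rests on feasibility and mortality precision, and subgroup analyses are done only if applicable. That stands, and it limits the consequence.

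**Conclusion.** The point holds as a fault in the stated rule. It has no route for ordered variables, and its default for NYHA class fits neither the comparison between comorbidity groups nor the within-patient comparison with baseline. Neither conclusion depends on a power figure.

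The power loss is illustrative: roughly 5 to 17 points under a uniform shift of OR 1.6 to 2.0 with 75 to 200 of 450 patients in the subgroup, little for very small or large effects, and a reversal for differences in shape. NYHA is an unpowered secondary outcome, so the consequence is modest, but the correction is cheap and worth making.

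**What to change.** Replace the categorical-variable sentence with text along these lines:

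*Chi-Square or Fisher exact tests will be used for nominal and binary variables in independent groups. NYHA class will be compared between patients with and without each comorbidity at each follow-up by a proportional-odds model adjusted for baseline NYHA class, reporting the common odds ratio with 95% CI. Within-patient change in NYHA class from baseline will be tested with the Wilcoxon signed-rank test or the sign test.*

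A rank-sum test at each follow-up is the simple version of the group comparison. The baseline-adjusted model is preferable: if patients with a comorbidity start in worse classes, an unadjusted comparison mixes that difference with the outcome.

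The cost is two or three sentences. No new data are needed, since NYHA is already recorded at baseline and at years 1, 3 and 5, and the methods are available in SPSS and R. The proportional-odds assumption must be checked, and power is lower for differences that are not a consistent shift. The class distribution by group should therefore still be tabulated.

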### Appreciation of the study design

IMPACT is a prospective, multicenter European registry, involving centers from Austria, Germany, The Netherlands and Switzerland. The multinational nature of this registry will increase the applicability of its findings to other European and international countries. Due to financial limitations, there is no control group with other types of bioprosthetic valves, making a comparison of valve types or valve generations impossible. However, long-term follow-up data with an assessment of patient outcomes and valve deterioration are scarce; an investigation into the impact of comorbid conditions in patients undergoing valve replacement is valuable and will enable the responsible use of this valve type in clinical practice. Furthermore, comparison between bioprosthetic valves and mechanical valves is beyond the scope of this registry. The multicenter design necessitated the establishment of a uniform assessment of SVD to be used over the 5-year follow-up. While five years is a considerable time-span for the study to judge mortality, it is also possible that early signs of valve deterioration may occur during this timeframe. This study has been designed in such a way that, with appropriate financial support, it can be extended beyond the proposed 5-year follow-up should it be possible to achieve reasonable data completeness. Data completeness, however, can be challenging in these patients when the survival for patients aged ≥75 years post SAVR with a bioprosthesis is 6–7 years [33]. It was not possible to establish an MCST CoreLab, as per the RESILIENCE trial, as this would have violated the non-interventional nature of the IMPACT registry and MSCT is not the standard-of-care for all sites used in this registry. Where MSCT is used in routine practice, this data is documented. Finally, the same INSPIRIS RESILIA valve will be used in all patients in the INDURE registry which will abolish any bias introduced by the use of different bioprosthetic valves.

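### Kaplan-Meier is named for safety outcomes that have death as a competing event, so the reported absolute risks will be too high, and more so in subgroups with higher mortality

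*Protocol article*

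**What the plan says.** The Statistical analysis section commits to one estimator: "Kaplan-Meier analyses will be performed for survival and safety outcomes". It does not limit this to all-cause death. The only other event methods it names are optional: "Linearized rates and actuarial probability statistics may be used where appropriate for adverse event reporting". It mentions no cumulative incidence or other competing-risk estimator.

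Table 1 shows what counts as a safety outcome. The exploratory VARC-2 safety list contains SVD, valve thrombosis, endocarditis, bleeding, "Re-intervention", "Cardiac-related mortality" and "Valve-related mortality", as well as all-cause mortality. Cardiac- and valve-related mortality are also secondary objectives, overall and by comorbidity subgroup.

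The analyses are to be run for the whole population and for the comorbidity subgroups where applicable. The Discussion (Comorbidities) describes comorbidity as an independent risk factor for death at 1 and 3 years after SAVR. Under Appreciation of the study design, the article adds that "the survival for patients aged ≥75 years post SAVR with a bioprosthesis is 6–7 years".

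**The concern.** A patient who dies can no longer have a re-intervention, endocarditis or a later death from a different cause. Applied to such an event, Kaplan-Meier ordinarily censors the patient at death. One minus the curve then estimates the risk in a hypothetical setting where nobody dies of anything else. It is not the share of implanted patients who go on to have the event, and it is always at least as large as that share.

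Two consequences matter here:

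- The excess depends on competing mortality. The article itself expects comorbidity to raise mortality, so absolute risks in different subgroups would be inflated by different amounts. The registry is meant to inform patient selection, for which absolute risk is a natural quantity to read.
- Curves of 1-KM for cardiac and non-cardiac death will add up to more than all-cause mortality, which is the primary endpoint.

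**Working it through.** **The plan's own figure.** The article gives 95% half-widths of ±0.87 and ±1.50 for observed rates of 1% and 3% with 500 patients. The Wald formula 1.96 × √(p(1−p)/500) gives ±0.872 and ±1.495 percentage points, so both reproduce. They concern the primary endpoint and are not in dispute.

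**Inputs from the article.** Follow-up is 5 years. Planning mortality is 1.2% at year 1 and 2.0% at year 2. Survival at age 75 or over is 6–7 years.

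**Assumptions.** Hazards are constant. The event hazard is h = 1% per year. The article gives no event rates and no mortality by subgroup, so the death hazard d is varied:

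- *Planning level.* The two-year average is −ln(0.980)/2 = 1.0% per year, and the second-year hazard is ln(0.988/0.980) = 0.8% per year. The value 0.9% lies between them.
- *Intermediate.* 4% per year, with no source in the article.
- *High.* If 6.5 years is an exponential median, d = ln 2/6.5 = 10.7% per year.

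**Formulas.**

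- 1-KM = 1 − exp(−5h) = 1 − exp(−0.05) = 4.88%, whatever d is.
- Cumulative incidence = h/(h+d) × [1 − exp(−5(h+d))].

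| Death hazard per year | 5-year mortality, 1 − exp(−5d) | Cumulative incidence | Excess of 1-KM, points | Ratio |
|---|---|---|---|---|
| 0.9% | 4.4% | 0.01/0.019 × (1 − e^−0.095) = 4.77% | 0.11 | 1.02 |
| 4% | 18.1% | 0.01/0.05 × (1 − e^−0.25) = 4.42% | 0.45 | 1.10 |
| 10.7% | 41.3% | 0.01/0.1166 × (1 − e^−0.583) = 3.79% | 1.09 | 1.29 |

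**Range for the last row.** Medians of 7 and 6 years give 3.85% and 3.71% (ratios 1.27 and 1.31).

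**Timing.** If the event has a 1-KM of 5% and occurs only in years 3 to 5, as might be assumed for a late valve failure, the ratios are 1.04, 1.20 and 1.52 at 5-year mortality of 4.9%, 20% and 41%.

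**Additivity.** Split the 10.7% death hazard into an assumed 5.0% cardiac and 5.7% non-cardiac.

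- 1-KM: (1 − e^−0.25) + (1 − e^−0.285) = 22.1% + 24.8% = 46.9%.
- All-cause mortality: 1 − e^−0.535 = 41.4%.
- Cumulative incidences: (5.0/10.7) × 41.4% = 19.4% and (5.7/10.7) × 41.4% = 22.1%. These sum to 41.4% before rounding.

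**The case against.** The strongest reply is that Kaplan-Meier answers a legitimate question. In the example every subgroup has the same event hazard, and 1-KM shows the same 4.88% in each. That correctly says comorbidity does not change the rate at which valves fail. Cumulative incidence would show 3.79% in the group with most deaths, which a careless reader could take for better durability. This stands. A reader might infer that the plan invalidates every subgroup comparison of valve outcomes. It does not: comparing cause-specific hazards censors deaths by design and is sound. Only absolute risks, and differences or ratios of them, are affected.

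Other points that stand:

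- The primary endpoint is all-cause mortality, for which Kaplan-Meier is appropriate. It is also appropriate for event-free-survival composites that count death as an event.
- "Freedom from valve-related rehospitalization" is a secondary clinical outcome and is not on the safety list. The article does not say that it will be analysed by Kaplan-Meier, so the point reaches it only if it is handled as time to event.
- The high-mortality figure comes from patients aged 75 or over, while the subgroups are defined by comorbidity. A reader might take the 29% excess as a forecast for, say, the kidney disease subgroup. The article gives no basis for that.
- Even the 1.09-point gap is smaller than the 95% half-width for a 5% event in all 500 patients, 1.96 × √(0.05 × 0.95/500) = 1.9 points. Unlike sampling error, however, the gap always runs in one direction and does not shrink with more patients.
- SVD is detected at scheduled echocardiograms, so its onset is known only to lie between visits. The continuous-time formula is a simplification for SVD, and cumulative incidence alone does not resolve that.

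The argument that the matter belongs in an unseen analysis plan is weaker. Such a plan may well add a competing-risk method, and the article does not spell out how deaths are handled. But the article is not silent: it names an estimator for these outcomes, and that estimator does not give the proportion affected.

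**Conclusion.** The point holds for absolute risks. For SVD, re-intervention, endocarditis, valve thrombosis, bleeding, and cardiac- and valve-related death, 1-KM will overstate the proportion of patients with the event, and more so in subgroups with higher mortality. Cause-specific curves will not sum to all-cause mortality.

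The size depends on mortality. At about the planning level it is roughly 0.1 percentage point on an event of about 5%, which is negligible. At assumed death hazards of 4% to 10.7% per year it is roughly 10–30% relative, and larger if events come late. The direction does not depend on these values. The magnitudes rest on constant hazards, an assumed event rate, and reading the 6–7 years as an exponential median.

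This is a correction worth making before the 5-year analysis. It does not threaten the primary result.

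**What to change.** Replace the single Kaplan-Meier sentence with a rule by type of outcome:

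- Kaplan-Meier for all-cause mortality and for event-free-survival composites.
- Aalen-Johansen cumulative incidence for the other time-to-event safety outcomes, with death (or, for cause-specific mortality, other-cause death) as the competing event. The same applies to any other non-fatal outcome analysed as time to event, including rehospitalization if it is handled that way.
- Subgroup comparisons through cause-specific hazards, for example cause-specific Cox models, shown beside the cumulative incidences so that lower incidence due to more deaths is not read as better durability.
- Any 1-KM curve for a valve outcome labelled as a net, death-censored estimate of device durability.

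The cost is a short change of text and slightly more analysis work. The methods are standard in R, which the article already names, and no new data are needed because deaths are already collected. The one real downside is less direct comparability with earlier valve series reported by Kaplan-Meier or actuarial methods; a labelled net curve would largely preserve it.
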